[figure not shown][figure not shown]

| Protocol History |             |                |                                                                                                                                                                                                                                                                                                                                                                                                                                                                                                                                                                                                                                                                                                                                                                                                                                                           |
|-------------------------|-------------|----------------|-----------------------------------------------------------------------------------------------------------------------------------------------------------------------------------------------------------------------------------------------------------------------------------------------------------------------------------------------------------------------------------------------------------------------------------------------------------------------------------------------------------------------------------------------------------------------------------------------------------------------------------------------------------------------------------------------------------------------------------------------------------------------------------------------------------------------------------------------------------|
| Version          | Date | Author  | Reason                                                                                                                                                                                                                                                                                                                                                                                                                                                                                                                                                                                                                                                                                                                                                                                                                                             |
| 1.0                     | 14/10/2014  | [name] | New protocol from draft                                                                                                                                                                                                                                                                                                                                                                                                                                                                                                                                                                                                                                                                                                                                                                                                                                   |
| 1.1                     | 09/03/2015  | [name] | Addition of investigators and sites                                                                                                                                                                                                                                                                                                                                                                                                                                                                                                                                                                                                                                                                                                                                                                                                                       |
| 2.0                     | 01/05/2015  | [name] | Change to sites, sample size estimate, addition of 5 quality of life survey items to enable cost-utility analysis, and confirmation that sites can continue to use an existing screening tool where this is working well                                                                                                                                                                                                                                                                                                                                                                                                                                                                                                                                                                                                                                  |
| 2.1                     | 27/07/2015  | [name] | Change to enable project staff to assist local site staff in collating and entering screening data and demographic and contact details; inclusion of cancer type as a self-reported item on the screening survey; removal of cancer stage from the screening dataset; clarification of written informed consent process                                                                                                                                                                                                                                                                                                                                                                                                                                                                                                                                   |
| 3.0                     | 11/11/2015  | [name] | Change of wording to baseline screening tool and removal of quality of life measures at baseline;
Change to cost effectiveness analysis;
Clarification of patient eligibility in relation to diagnosis of cancer;
Clarification of the role of interpreters;
Addition of a letter of approach to patients;
Small changes to wording within the letter of approach to carers;
Amendments to PISCFs to reflect above changes and to add script about Medicare and Pharmaceutical Benefits Scheme (PBS) information about data collection, as per the requirements of the Australian Government Department of Human Services;
Participant information sheets, consent forms and letters of approach have been removed as Appendices to allow for version changes that have occurred and may occur throughout the duration of the trial. |
| 3.1                     | 17/12/2015  | [name] | Change to the processes of data entry by site staff and secure transfer of baseline screening data from study sites to the project team.                                                                                                                                                                                                                                                                                                                                                                                                                                                                                                                                                                                                                                                                                                                  |
|                         |             |                |                                                                                                                                                                                                                                                                                                                                                                                                                                                                                                                                                                                                                                                                                                                                                                                                                                                           |
| 4.0                     | 16/08/2016  | [name] | Change to consent processes for patient- and caregiver secondary data;                                                                                                                                                                                                                                                                                                                                                                                                                                                                                                                                                                                                                                                                                                                                                                                    |

|     |            |                |                                                                                                                                                                                                                                                                                                                                                                                                     |
|-----|------------|----------------|-----------------------------------------------------------------------------------------------------------------------------------------------------------------------------------------------------------------------------------------------------------------------------------------------------------------------------------------------------------------------------------------------------|
|     |            |                | Addition of a sustainability phase (including change to Figure 1);
Updates to investigator titles;
Removal of reference to consent withdrawal form attached pg. 28 of protocol_V3.1 to adhere to HREC documentation                                                                                                                                                                           |
| 5.0 | 05/04/2017 | [name] | Request for word change to pain screening document to identify where the project team came from and variation in information required by health professional;
Change wording in protocol section 9.2 Appendix (pg 44) to reflect new wording on screening form;
Add new site investigators and update place of work for investigators;
Remove erroneous words from the document on page 45 |
| 5.1 | 22/08/2018 | [name] | Update the names of the site investigators;
Update of protocol history                                                                                                                                                                                                                                                                                                                           |

## TRIAL SUMMARY

### Background

Pain is a common and distressing symptom in people with cancer that is under-treated. Better management of pain has the potential to improve quality of life for most people with cancer and reduce healthcare costs by avoiding unnecessary hospital admissions, supporting non-pharmacological approaches and quality use of medicines, and reducing caregiver distress.

International studies have found that guidelines and clinical pathways can improve the quality of care for cancer pain and patient outcomes, but implementation is challenged by barriers at the levels of the healthcare system, provider and patient. Evidence supports implementation of guidelines by means of health professional and patient education and audit and feedback.

### Aim

To evaluate the effectiveness and cost-effectiveness of a suite of strategies designed to implement Australian clinical practice guidelines to improve pain outcomes in adult outpatients with cancer in metropolitan, regional and rural oncology and palliative care settings.

### Study design

The trial will use a stepped-wedge cluster randomised controlled design wherein participating services will take turns in introducing the strategies so that outcomes can be compared before and after the change in practice.

A qualitative sub-study will use semi-structured interviews and focus groups to investigate aspects of the intervention that have worked well or could be improved from the perspectives of patients, carers and centre staff.

I001/ 4th September 2018

## **Control and intervention arms**

### **Control arm**

Whilst in the control arm, participating centres will be provided with an electronic or paper-based system for screening patients for worst and average pain severity via a 0-10 numerical rating scale (NRS). Centres that are already using a different tool for screening symptoms will continue to use the same tool where this is preferred, with addition of screening items for pain as necessary. Screening tools and patient-held resources will be translated to support communication by non-English speaking patients, who are at special risk for poor outcomes. Staff at the centre will be at liberty to use the pain screening data in any way they wish.

### **Intervention arm**

During a training phase, designated 'champions' and staff at each centre will attend workshops to learn about the project and how to tailor implementation strategies to their centre's needs. Implementation strategies will include:

1. An audit tool to enable centres to monitor how well they are implementing core standards of cancer pain assessment and management;
2. Tools for identifying barriers and facilitators to cancer pain screening, assessment and management and strategies to overcome barriers;
3. QStream online health professional education to test and consolidate knowledge of cancer pain assessment and management;
4. Patient-held resources to ensure management remains centred on individual patient needs, support patient-health professional communication and coordination and help patients advocate for evidence-based, person-centred care;

In the intervention phase, implementation strategies will be put in place and monitored. A community of practice between staff at different centres implementing the strategies will be facilitated by means of regular teleconferences, chaired by a project team member.

## **Sites and participants**

Sites will be outpatient services at oncology and palliative care centres. Participants will include patients, carers and centre staff at each site.

Inclusion criteria for patients to be included in the primary endpoint will be: 1) attending a participating cancer centre as an outpatient during the study period; 2) having a diagnosis of current active cancer; 3) being able to self-complete a 0-10 NRS for severity of worst and average pain in English, Chinese, Italian, Greek, Vietnamese or Arabic; 4) choosing not to opt-out of being contacted 1 week later to complete the NRS over the telephone and giving verbal consent to do so when telephoned; 5) a score of moderate-severe ( $\geq 5$ ) on the NRS for worst pain.

Inclusion criteria for patients contributing to secondary outcomes will be meeting inclusion criteria 1, 2, 3 and 4 above and also: 5) a score  $\geq 2$  on the NRS for worst pain; 6) providing verbal informed consent in English; 7) having spoken and written English proficiency sufficient to complete study measures.

Inclusion criteria for carers will be: 1) being identified by a patient who has given verbal informed consent to participate in the study as providing them with substantial emotional and practical support in an unpaid capacity; 2) providing verbal informed consent; 3) having spoken and written English proficiency sufficient to complete a brief survey and/or interview.

Inclusion criteria for centre staff will be: 1) being employed on a permanent basis either full- or part-time at a participating oncology or palliative care centre in a role that provides clinical care to patients with cancer pain or front desk, client-focused administrative support; 2) providing written informed consent.

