## **Objectives**

### Primary objective

To evaluate the ability of the intervention versus control arm to increase the probability that patients screened as having moderate-severe ( $\geq 5$ ) worst pain will experience a clinically important improvement of 30% on a 0-10 NRS 1 week later.

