#### 3.2.1 Patients

##### 3.2.1.1. Inclusion criteria for patients contributing to primary outcome

- 1) Attend a participating oncology and palliative care centre as an outpatient during the study period
- 2) Have a diagnosis of current active cancer
- 3) Be able to self-complete a 0-10 numerical rating scale (NRS) for severity of worst and average pain in English, Chinese, Italian, Greek, Vietnamese or Arabic)
- 4) Choose not to opt-out of being contacted 1 week later to complete the NRS and give verbal consent to do so.
- 5) Score  $\geq 5$  on the NRS for worst pain

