### 660 **3.6 Randomisation**

661 Randomisation will be concerned with the time at which each centre transitions from the control  
662 arm to training and intervention. Stratification will be unnecessary because each centre will serve as  
663 its own control. Patients will be automatically allocated to usual care or intervention arms  
664 according to the current arm of their treatment centre upon their first presentation. Participants will  
665 be sequentially allocated an ID number, which will be used for all subsequent study documentation  
666 for that participant.

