#### 5.1.2.1 Consent process

This study will use four procedures relating to consent:

1. A waiver on patient consent to use de-identified screening and audit data for endpoints comparing average pain and adherence to key standards of cancer pain assessment and management within the patient population during intervention and sustainability versus control periods;
2. An opt-out procedure for patient permission to obtain their contact details to telephone them 1 week later about the research for the primary outcome of worst pain on a 0-10 NRS 1 week after a positive screen. Upon contact, patients will be invited to give verbal consent to provide primary outcome data but will still be at liberty to refuse at that time;
3. A verbal informed consent procedure for secondary outcome data (surveys, interviews and medical record audit);
4. A written informed consent procedure for involvement by patients in the study's health economic evaluation.

The National Health and Medical Research Council (NHMRC) National Statement on Ethical Conduct of Research (2007) includes provision for waiving and an opt-out approach to consent in Chapter 2.3 (45).

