#### 5.1.2.2 Waivered consent

A waiver on consent will be sought to use pain screening data to compare patient populations between centres at baseline and to see whether this population is changed in terms of pain by the intervention. As well as screening data, a waiver on consent will be requested to collect data on age, gender and cancer type to contextualise screening data, compare patient characteristics between centres and establish the representativeness of samples for primary and secondary outcome assessment. These data will be extracted by local staff or project staff. Screening measure data will be entered onto an Excel spread-sheet by local or project staff. For patients who score  $\geq 2$  and who do not opt out, their name and contact details will be entered onto the spread-sheet. Names and contact details for those patients who score NRS 0-1 for worst pain or who opt out of being contacted will not be entered onto the spread-sheet.

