#### 5.1.2.3 Opt-out procedure

In the opt-out procedure, patients will indicate consent to be contacted 1 week after screening positive for a pain NRS to be administered if they do not tick a box of the screening survey to request that this should not occur. The screening form will include information about the project and that patients will be contacted at the centre or via telephone 1 week later about their pain if they do not tick the box. When the contact is made, the researcher will identify who they are, explain why they are contacting the patient and the purpose of this information, together with reassurance regarding confidentiality to ensure the participant still wishes to continue (Appendix 3). Patients will be given the opportunity to provide verbal consent to provide primary outcome data but will still have the option of refusal at that time. The opt-out procedure has been chosen because, when evaluating a health system level intervention, selection bias in the primary outcome would substantially impact on the ability to interpret the true efficacy of the intervention. The data being requested of participants is minimal and poses minimal risk to the participants. Where patients report pain  $\geq 2$  at this follow-up contact, they will be provided with contact details for their medical team to follow up if they so wish. Patients will be deemed lost to follow-up if they have not

899 provided pain NRS data of been given an alternative day/time to make contact after 3 attempts to  
900 contact on 3 consecutive days.

901

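### Verbal consent at the week-1 outcome contact is a condition of entry to the primary population, although the objective concerns all patients screened at 5 or more

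*Protocol*

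**What the plan says.** **Entry rule.** In the Trial Summary (Sites and participants), criterion 4 for the primary endpoint requires not opting out and "giving verbal consent to do so when telephoned". Section 3.2.1.1 repeats it without the reference to the call: "Choose not to opt-out of being contacted 1 week later to complete the NRS and give verbal consent to do so".

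**Timing of consent.** Section 5.1.2.1 says: "Upon contact, patients will be invited to give verbal consent to provide primary outcome data but will still be at liberty to refuse". Section 5.1.2.3 (Opt-out procedure) describes the same request at the week-1 contact, and the Sample size paragraph of the summary places recruitment at week 1. Section 5.1.1.1 is less clear: it can be read as seeking agreement first and the rating a week later.

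**Target population.** The primary objective is to "increase the probability that patients screened as having moderate-severe" worst pain achieve a 30% improvement. Sections 2.2.1 and 5.2.1 define the population the same way, with no condition on being reached.

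**Allocation.** Patients belong to an arm "according to the current arm of their treatment centre upon their first presentation" (3.6).

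**Losses.** Section 5.1.2.3 classes patients not reached after three attempts as lost to follow-up. Section 5.5.2 allows for 20% dropout of patients.

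**Reason for opt-out.** Section 5.1.2.3 explains that "selection bias in the primary outcome would substantially impact on the ability to interpret the true efficacy of the intervention".

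**The concern.** Whether a patient belongs to the primary population is settled about a week after exposure to the centre's arm. It is settled at the contact where the outcome is collected, by research assistants whom section 3.7 says cannot practicably be blinded. The responder rate then describes patients alive, reachable and willing at week 1, not all those screened at 5 or more.

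Two things are at stake. First, both rates may be shifted relative to the stated target. Second, if the intervention changes who answers or agrees, the arms differ through selection after exposure, which is what the opt-out procedure was meant to prevent. An analysis plan can say how to handle missing outcomes, but it should not have to treat as missing those patients whom the protocol defines as ineligible.

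**Working it through.** **1. The passages side by side**

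| Patient screened at 5 or more, no opt-out | Under criterion 4 | Elsewhere in the protocol |
|---|---|---|
| Not reached at week 1 | Not eligible | Lost to follow-up (5.1.2.3); dropout (5.5.2) |
| Reached, refuses | Not eligible | Free to refuse (5.1.2.1, 5.1.2.3); not clearly covered by the loss-to-follow-up rule |
| Died before week 1 | Not eligible, as consent is impossible | Death foreseen in the 4-week study period (5.2) |
| All of these | Outside the primary population | Inside the population of the objective and outcome (2.2.1, 5.2.1) |

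**2. The plan's own figures**

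Section 5.5.2 gives 82 × 6 = 492 evaluable patients and 8 × 100 = 800 recruited, with a margin of 100 − 82 = 18 per site for drop-out. The arithmetic is right. The stated power above 90%, for a 0.5 SD difference on a continuous score, is also plausible: a Hussey–Hughes stepped-wedge calculation (6 centres, 7 equal periods, 82 per centre) gives 0.96, 0.93 and 0.93 for assumed intra-class correlations of 0.01, 0.05 and 0.10. The power figure is not the problem. The margin is: if patients enter only by agreeing to give the week-1 score, there is almost no primary-outcome drop-out for the 18 to cover. It is then unclear whether the 100 per site are patients screened or patients with a score.

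**3. Size of a possible bias**

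Let q be the proportion of an arm not entering, and g the amount by which non-entrants' responder rate falls below entrants'. The rate in all screened patients equals the entrants' rate minus q × g. The difference among entrants therefore exceeds the difference among all screened by

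bias = q1 × g1 − q0 × g0, which is (q1 − q0) × g when the gap is the same in both arms (1 = intervention, 0 = control).

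The protocol gives no week-1 rate of non-contact, refusal or death, so all inputs below are assumptions.

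- Equal q and equal g: bias = 0.
- q1 = 25%, q0 = 15%, g = 30 points: 0.10 × 0.30 = 0.03, or 3 points in favour of the intervention. With 400 per arm, non-entry is 100 + 60 = 160, which is 20% of 800 and so matches the overall dropout allowance.
- The same with the arms reversed: 3 points against the intervention.
- q1 = 30%, q0 = 10%, g = 30 points: 0.20 × 0.30 = 0.06, or 6 points.

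A harsher case assumes no true effect, with 40% of all screened patients responding in each arm and every non-entrant a non-responder:

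| Non-entry, control / intervention | Rate among entrants | Spurious difference |
|---|---|---|
| 20% / 20% | 0.40/0.80 = 50.0% in both | 0 |
| 20% / 30% | 50.0% vs 0.40/0.70 = 57.1% | +7.1 points |
| 20% / 10% | 50.0% vs 0.40/0.90 = 44.4% | −5.6 points |

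The first row shows that equal non-entry leaves the comparison intact under these assumptions but raises both rates from 40% to 50%.

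**4. Bounds with equal 20% non-entry**

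Suppose entrants respond at 40% (control) and 50% (intervention). Counting non-entrants as non-responders gives 0.8 × 50% − 0.8 × 40% = 8 points. The extremes are 40 − (32 + 20) = −12 points and (40 + 20) − 32 = +28 points.

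**The case against.** The strongest reply is that this is loose wording in an eligibility list. Section 3.2.1.1 omits the mention of the call, section 5.1.1.1 can be read as seeking consent earlier, and sections 5.1.2.3 and 5.5.2 already treat unreached patients as losses. That shows the documents are mixed. It does not remove the conflict: the summary, the Sample size paragraph and both consent sections point to week 1.

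Second, the protocol has safeguards. Section 5.1.1.1 keeps a Participant Master Index of patients scoring 2 or more, with reasons for non-entry. Under 5.1.2.2, "a waiver on consent will be requested to collect data on age, gender and cancer type to contextualise screening data", and the same sentence adds a check on how representative the primary sample is. Recruitment follows the same flow in both arms, and section 3.7 calls for standardised data collection and tells patients only the general aims. These deserve credit, and they make the fix cheap. But they describe selection without putting those patients back in the denominator.

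Third, relabelling yields no extra scores, because nobody can supply one without agreeing, and the imputation or weighting model belongs in an analysis plan. Both points stand. What belongs in the protocol is who is in the population.

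Fourth, the waiver's stated purposes do not include adjusting the primary analysis. This stands and is part of the cost.

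**Conclusion.** The concern holds as a conflict over the primary denominator. Criterion 4, on its most natural reading, makes entry depend on consent at the outcome contact. The objective, the allocation rule, the loss-to-follow-up rule, the dropout allowance and the reason for opt-out all imply a population fixed at screening. This should be corrected.

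The size of any bias cannot be derived from the protocol. The 3-point figure rests wholly on an assumed 10-point imbalance in non-entry and an assumed 30-point responder gap.

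Three stronger readings are tempting but unsupported:

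- A reader might infer that patients admitted to hospital are excluded. No criterion says so, and contact may be by telephone, so admission matters only if it prevents contact or agreement.
- A reader might infer that the comparison is biased. That requires non-entry or the responder gap to differ between arms, and the protocol gives no figure for either.
- A reader might infer a settled intention to drop unreached patients. Sections 5.1.2.3 and 5.5.2 suggest otherwise.

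**What to change.** 1. Define the primary population at screening: criteria 1, 2, 3 and 5, no opt-out box ticked, and the exclusions in 3.3.1 unchanged. Keep verbal consent as a condition only for collecting the week-1 score.
2. Reconcile Sites and participants, 3.2.1.1, 5.1.1.1, 5.1.2.3 and 5.5.2 on when consent is sought, how a refusal at week 1 is classed, and whether the 100 per site are patients screened or patients with a score.
3. Treat non-contact, refusal and death before week 1 as missing outcomes or intercurrent events under a stated rule, and report each by arm from the Participant Master Index.
4. Adjust the primary analysis for the screening score and the other variables held under the waiver (age, gender, cancer type), with a sensitivity analysis counting missing as non-response. The exact imputation or weighting model can be left to the analysis plan.

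The cost is a rewording, a modest extra analysis on data already collected, and confirmation from the ethics committee that the waiver covers this use of non-consenters' de-identified screening data. No patient is asked for anything more.
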